### Participants

We will include all patients 18 years of age or older admitted to the ICU for at least 24 hours who have a prescription for EN or are receiving NIPPV for greater than 48 hours. Patients who received majority NIPPV for 48 hours at any one time will also be included even if they were not prescribed EN. EPIC Hyperspace is now the Electronic Medical Record (EMR) used in hospitals in Hamilton. We will include patients admitted to the ICU since EPIC went live at each site. For St. Joseph’s Hospital Hamilton (SJHH) this is between January 1, 2018, and December 31, 2023. For the two sites at Hamilton Health Sciences (HHS), this is between June 4, 2022, and December 31, 2023. Exclusion criteria includes patients receiving only nocturnal NIPPV, patients who have had gastrointestinal surgery in the month preceding ICU admission, and patients who have confirmed or suspected luminal obstruction on admission. For the purposes of this study NIPPV will exclude high flow nasal canula (HFNC).

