### Data collection

Data will be collected using the search function of EPIC Hyperspace and assistance from HHS and SJHH Information Technology (IT) services teams. The MRN numbers of patients meeting the inclusion criteria will be identified. The data will be exported directly to excel. Any missing data from IT reports will be entered via manual chart review. For each recruited patient, the following baseline characteristics will be recorded to determine factors associated with intolerance of IEN or CEN and with the development of ICU-acquired diarrhea. The baseline characteristics will include demographic data, anthropometric data, clinical data on Day 1 of ICU stay (surgical, medical vs trauma admission, diagnostic category, admitting diagnosis, ventilation status, inotrope/ vasopressor use, renal replacement therapy), admitting hospital, medical comorbidities (prior GI disease, previous luminal surgeries), nutritional assessment (caloric goals on admission will be determined using weight and registered dietician assessment), antibiotic prescription on admission and serum albumin on ICU admission. Table 1 outlines the primary and secondary outcomes as well as the data that will be recorded each day of the ICU admission up until the 30th day or ICU discharge. This includes mode of nutrition (IEN, CEN, oral, or PN), daily caloric intake, mode of ventilation (Invasive, NIPPV), presence of diarrhea, bacteremia greater than 48 hours after admission (gram-positive bacilli and coagulase-negative staph will be reviewed and omitted if team feels it is more likely contaminant), incidence of aspiration pneumonia/pneumonitis, *Clostridioides difficile* infection (CDI), presence of vomiting, ileus or abdominal distention, vasopressor/inotrope dose, average daily insulin dose and blood glucose, survival status in ICU, ICU length of stay. Survival to hospital discharge and hospital length of stay will be collected for the entire hospital stay.

**Table 1 pone.0322122.t001:** Statistical Plan.

Research Objectives	Outcome	Covariates/Subgroups	Analytical Approach
To determine the incidence of diarrhea amongst patients on IEN and CEN	WHO-defined diarrhea	N/A	Descriptive statistics (proportion of patients with diarrhea) and corresponding 95% CI

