To determine risk factors associated with diarrhea during ICU admission	**Dependent Variable** WHO-defined diarrhea	Age, sex, type of nutrition (IEN/CEN), antibiotics, GI comorbidities, vasopressor/inotropes, daily caloric intake, NIPPV, surgical/trauma/medical admission	Logistic Regression
Secondary Outcomes			
**Research Objectives**	**Outcome**	**Covariates/Subgroups**	**Analytical Approach**
To determine whether IEN or CEN is better for reaching caloric requirements during ICU stay	**Dependent Variables:** Average caloric intake (percent goal determined by RD or 25 kcal/kg) at 48 hours and 7 days after initiation of CEN/IEN Proportion of patients on PN at 48 hours and 7 days after initiation of CEN/IEN	NIPPV, Age, sex, antibiotics, GI comorbidities, type of nutrition (IEN/CEN) vasopressor/inotropes, daily caloric intake, surgical/trauma/medical admission	Descriptive statistics (average caloric intake) and corresponding 95% CI Descriptive statistics (proportion of patients on PN) and corresponding 95% CI Logistic regression
To determine whether IEN or CEN is associated with ICU-acquired bloodstream infection or *Clostridium difficile* infection	Incidence of positive blood cultures drawn at least 48 hours after admission, excluding coagulase-negative staphylococcus unless suspected by ICU team to not be contaminant.	NA	The incidence of bloodstream infections will be computed as the number of new cases during ICU stay divided by the person-time at risk. Descriptive statistics (proportion of patients with ICU-acquired bloodstream infection or *C. difficile infection*) and corresponding 95% CI
To determine whether IEN or CEN is associated with differences in mortality or length of stay (ICU or hospital)	**Dependent Variables** Mortality (ICU and hospital) Length of stay (ICU and hospital)	Age, sex, type of nutrition (IEN/CEN), antibiotics, GI comorbidities, vasopressor/inotropes, daily caloric intake, NIPPV, surgical/trauma/medical admission	Descriptive statistics (mortality and length of stay) and corresponding 95% CI Logistic regression

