For the secondary outcomes patients also be divided into those who have received NIPPV and those who have not. For the purposes of this study, NIPPV will exclude HFNC but will include bilevel positive airway pressure (BiPAP) and continuous positive airway pressure (CPAP) delivered via any interface. To evaluate the relationship between IEN, CEN and NIPPV on caloric goals, each patient’s caloric intake at 48 hours and 7 days will be divided by their 24 hour caloric target (as determined by RD assessment and by the algorithm 25 kcal/kg) (Table 1). The average of these percentages with associated 95% CI will be calculated in each group. The proportion of patients in each group receiving supplement parenteral nutrition at these time points will also be determined to help evaluate the effectiveness of each EN strategy (Table 1). Logistic regression will also be applied to evaluate the role of covariates; specifically baseline characteristics and the effect they may have on patients reaching their caloric targets (Table 1). In terms of other secondary outcomes, the incidence of hospital acquired infections, ICU and hospital mortality will be determined per person-time at risk in each group (IEN vs CEN) with associated 95% CI. Significant differences between groups will again be determined by two sample t-test. Multivariate logistic regression will evaluate associations between baseline characteristics and the type of EN chosen.

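### PN status at 48 hours and 7 days is used to judge IEN against CEN, but it does not separate PN already running when EN began from PN newly needed afterwards

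*Protocol article*

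**What the plan says.** The Table 1 row concerned serves the objective "To determine whether IEN or CEN is better for reaching caloric requirements during ICU stay". One of its dependent variables is "Proportion of patients on PN at 48 hours and 7 days after initiation of CEN/IEN". The approach listed is "Descriptive statistics (proportion of patients on PN) and corresponding 95% CI Logistic regression", with covariates "NIPPV, Age, sex, antibiotics, GI comorbidities, type of nutrition (IEN/CEN) vasopressor/inotropes, daily caloric intake, surgical/trauma/medical admission".

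The Data analysis section repeats the measure and gives its purpose: the proportion "receiving supplement parenteral nutrition at these time points will also be determined to help evaluate the effectiveness of each EN strategy".

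Eligibility is in the Participants section: "Exclusion criteria includes patients receiving only nocturnal NIPPV, patients who have had gastrointestinal surgery in the month preceding ICU admission", together with confirmed or suspected luminal obstruction on admission. PN before or at the start of EN is not mentioned there.

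The Data collection section includes "mode of nutrition (IEN, CEN, oral, or PN" among the items "recorded each day of the ICU admission up until the 30th day or ICU discharge". The Feasibility section adds that PN prescriptions are readily available from the electronic record.

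**The concern.** A measure meant to reflect how well a feeding strategy works should respond to what happens after that strategy starts. Status at a fixed time also carries what was there before. A patient bridged with PN who is still being weaned 48 hours after EN begins is on PN at that time, and neither IEN nor CEN caused that PN to be started. A patient who first needs PN on day 3 and is off it by day 6 is on PN at neither time.

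Feeding mode was not randomised. The Introduction cites guideline advice against IEN in high-risk patients, the Discussion says that institutional practice and practitioner comfort often decide the method, and the limitations paragraph concedes that differences may reflect covariates and severity of illness. PN at EN start could therefore differ between the groups for reasons unrelated to the strategy. A difference in PN use could then appear with no difference in new need, or a real difference could be hidden.

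**Working it through.** **Plan's own figure.** There is none for PN: no rate, power or sample size is given. The only sample-size figure, 455 per group, is for diarrhea (25.1% against 17.5%, two-sided alpha 0.05, power 0.80). The pooled-variance formula without continuity correction reproduces it. It has no bearing on this point.

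**Step 1: can the plan as written remove prior PN?**
- Exclusions (Participants): prior or current PN is not listed.
- Baseline characteristics (Data collection): PN at EN start is not listed.
- Covariates in the row (Table 1): PN at EN start is not listed, so the logistic regression, if applied to PN, would not adjust for it.
- The description of the PN as supplemental (Data analysis) does not help, because PN that continues alongside newly started EN is also supplemental.

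**Step 2: how carry-over enters the 48-hour proportion.** For one group let b be the share on PN at EN start, r the share of those still on PN at 48 hours, and n the share of the others who have started PN and are on it at 48 hours. Then

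P = b·r + (1 − b)·n.

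If r and n are the same in both groups, so that there is no difference in new PN,

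P(CEN) − P(IEN) = (b_CEN − b_IEN)·(r − n).

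All inputs are assumptions: r = 0.70, n = 0.05, and b varied.

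| b, IEN | b, CEN | P, IEN | P, CEN | CEN − IEN |
|---|---|---|---|---|
| 0% | 0% | 5.0% | 5.0% | 0 |
| 2% | 10% | 0.014 + 0.049 = 6.3% | 0.070 + 0.045 = 11.5% | +5.2 points |
| 5% | 10% | 0.035 + 0.0475 = 8.25% | 11.5% | +3.25 points |
| 10% | 2% | 11.5% | 6.3% | −5.2 points |

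Check on the second line: (0.10 − 0.02) × (0.70 − 0.05) = 0.052.

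Equal b is not enough if r differs. With b = 10% in both groups and r = 0.70 for CEN but 0.50 for IEN, the proportions are 11.5% and 0.050 + 0.045 = 9.5%, a gap of 2.0 points with the same new PN.

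**Step 3: PN between the two times.** Assume 10% of patients start PN after 48 hours. If 20% of them stop before day 7, the day-7 proportion counts 0.10 × 0.80 = 8%; if 40% stop, it counts 0.10 × 0.60 = 6%. PN started and stopped within the first 48 hours is missed as well.

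**Step 4: comparison inside Table 1.** Bloodstream infection must come from cultures taken at least 48 hours after admission and is counted as new cases over time at risk. Aspiration is also counted as new cases. The PN measure has neither a new-onset requirement nor an at-risk period.

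**The case against.** The strongest reply is that status at a time point is a coherent quantity. It sits beside percent of caloric goal at the same 48 hours and 7 days, and read together they show whether EN alone was enough at that moment. A patient still on earlier PN at 48 hours may show slow advancement of EN, which bears on the objective. This stands, and it is why the planned proportions should be kept. It does not make them a clean measure of effectiveness, because they mix that information with PN use that came before the strategy.

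Three stronger readings are tempting, and the protocol does not support them.

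- *The plan scores PN at these times as failure and its absence as success.* It uses neither term for this measure. It says only that the proportions help evaluate effectiveness.
- *The comparison will favour IEN, because high-risk patients receive both PN and CEN.* The guideline advice makes an imbalance plausible, but nothing in the protocol links PN at EN start to feeding group in this cohort. The assumed scenarios go both ways. The exclusions for recent gastrointestinal surgery and obstruction probably reduce prior PN, and covariates such as GI comorbidities and vasopressors may absorb part of any confounding.
- *The day-7 proportion is wrong because daily data end at ICU discharge.* Denominators and the handling of early death or discharge are details that a condensed article commonly leaves to a fuller plan, and the same question arises for day-7 caloric intake. It is not a separate error in the PN definition.

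**Conclusion.** The point holds in a limited form. Followed as written, the PN comparison cannot separate carried-over PN from new need, and it does not see PN courses that fall between the two times. This follows from the stated definition together with the exclusions, baseline list and covariates.

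The size and direction of any bias cannot be found from the protocol. The range of −5.2 to +5.2 points rests wholly on the assumed values of b, r and n. The carry-over bias is zero if prior PN is balanced between the groups and continues equally. PN is a supporting component of one secondary objective; the primary diarrhea outcome and its sample size are unaffected. The change is worth making because it is cheap and removes a baseline difference from a non-randomised comparison.

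**What to change.** In the caloric-requirements row of Table 1 and in the Data analysis section:

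1. For the comparison of effectiveness, define new PN as the first PN after EN initiation, cumulative to 48 hours and to day 7, among patients not on PN at EN initiation.
2. Add PN at EN initiation to the baseline characteristics and report it by group.
3. Keep the planned proportions on PN at 48 hours and 7 days as descriptive results.
4. Optionally, present new PN as a cumulative incidence with ICU death and ICU discharge as competing events.

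No new data are needed, since daily mode of nutrition and PN prescriptions are already to be extracted. The cost is a small extra analysis (somewhat more if the competing-event analysis is added) and a slightly smaller denominator. Patients being weaned from earlier PN drop out of the new-PN measure but remain visible in the retained proportions.

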## Discussion

EN has become the standard of care for nutritional support in most critically ill patients. Despite this, nutrition and the consequences of delivering it are discussed by multidisciplinary teams and often family members daily in the ICU. Abdominal pain, distention, vomiting, and diarrhea are frequent [11], and there is little to no high-quality evidence outlining which EN strategies best mitigate these risks. Institutional practices and practitioners’ comfort with specific strategies often dictate the EN method.

Diarrhea is a frequent problem amongst critically ill patients that is also understudied. It has been shown in a recent multicentre prospective study to affect greater than 38% of critically ill patients [12]. Moreover, diarrhea is particularly distressing to patients and their families and has been shown in several studies to be associated with increased length of stay. Selecting an EN strategy that would be less likely to result in diarrhea would be valuable to clinicians and patients alike.

Physiological studies have suggested the potential benefits of IEN over CEN [20]. This is despite CEN being more common than IEN in most critical care units [20]. In healthy volunteers, IEN causes more rapid gastric emptying, increased superior mesenteric arterial flow, and physiologic insulin peaks compared to CEN [20]. While caution should be used when generalizing these findings to critically ill patients, a small RCT of 120 patients did find that mechanically ventilated patients on IEN were more likely to meet caloric targets. Furthermore, interrupted feeds for procedures and loss of enteral access are more likely to affect the daily caloric intake amongst patients on CEN. With malnutrition still being a large problem in Canadian ICU, IEN may be a potential solution and led us to evaluate the effects of EN strategy on the daily caloric intake and PN [21]

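### Table 1 adjusts for daily caloric intake in all three logistic regression rows: this is circular for caloric intake and is post-exposure adjustment for PN, mortality, length of stay and diarrhea

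*Protocol article*

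**What the plan says.** Three rows of Table 1 name logistic regression as the analytical approach, and all three list daily caloric intake as a covariate.

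- **Caloric requirements.** The objective is "To determine whether IEN or CEN is better for reaching caloric requirements during ICU stay". One dependent variable is "Average caloric intake (percent goal determined by RD or 25 kcal/kg) at 48 hours and 7 days after initiation of CEN/IEN"; the other is the proportion on PN at the same two times. The covariates are "NIPPV, Age, sex, antibiotics, GI comorbidities, type of nutrition (IEN/CEN) vasopressor/inotropes, daily caloric intake, surgical/trauma/medical admission".
- **Risk factors for diarrhea, and mortality/length of stay.** Both rows give the list "Age, sex, type of nutrition (IEN/CEN), antibiotics, GI comorbidities, vasopressor/inotropes, daily caloric intake, NIPPV, surgical/trauma/medical admission".

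The Data collection section does not place caloric intake among the baseline characteristics. It belongs to "the data that will be recorded each day of the ICU admission up until the 30th day or ICU discharge". The Data analysis section describes the regression for caloric targets as evaluating covariates, "specifically baseline characteristics and the effect they may have on patients reaching their caloric targets", and points to Table 1. The Discussion cites a small RCT in which "mechanically ventilated patients on IEN were more likely to meet caloric targets", and says that such considerations "led us to evaluate the effects of EN strategy on the daily caloric intake and PN".

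**The concern.** An IEN/CEN coefficient can answer whether one feeding mode does better only if the model does not hold fixed the thing that feeding mode changes. In the caloric row the covariate is the outcome, or a near copy of it. If one mode really delivers more of the caloric goal, the adjusted model would tend to report no difference.

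For PN use, mortality and length of stay the fault is milder. Intake is not the outcome, but it is measured after feeding starts and the protocol itself regards it as a consequence of mode. Adjusting for it removes whatever part of the mode effect runs through intake. In the diarrhea model there is a second difficulty. Intake is recorded through the stay and diarrhea counts at any time in the index admission, so intake can follow diarrhea as well as precede it.

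**Working it through.** **1. No plan figure bears on this point.** The one computed design figure, 455 per group, reproduces. With 25.1% and 17.5%, two-sided 0.05, power 0.80 and pooled variance, (1.960·√(2·0.213·0.787) + 0.842·√(0.251·0.749 + 0.175·0.825))² / 0.076² = 454.4, which rounds up to 455. The covariate lists do not affect it.

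**2. Caloric row, algebra.** The Data analysis section forms the outcome as Y = I/T, where I is intake at 48 hours or 7 days and T is the 24-hour target. T comes from the dietician's assessment or 25 kcal/kg.

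- If the covariate is I for that day, then given I, Y varies only through T. The IEN/CEN coefficient then reflects differences in target between groups, not differences in delivery.
- If the covariate is an average of daily intake, the coefficient carries only the effect of mode on that day's departure from the patient's own average.

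Either way the delivery effect is largely conditioned out. How completely depends on how the daily series is summarized, which the article does not state.

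**3. Caloric row, illustration (all inputs assumed).** 200,000 simulated patients, half in each mode; mean daily intake 70% of goal with CEN, SD 20; IEN adds 8 points; day-7 intake is the patient's mean plus noise; the outcome is reaching 80% of goal on day 7. Mode acts only through mean intake.

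| SD of day-7 noise | IEN/CEN OR without intake | with intake |
|---|---|---|
| 5 | 1.88 | 1.00 |
| 10 | 1.78 | 0.99 |
| 20 | 1.57 | 0.99 |

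**4. Text against table.** The Data analysis section limits the caloric-target regression to baseline characteristics. Table 1 gives the same regression a covariate that Data collection lists as daily. Both cannot be followed.

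**5. Diarrhea model, illustration (all inputs assumed).** Direct log-odds of mode 0.30 (OR e^0.30 = 1.35); IEN shifts intake by 4, 8 or 12 points of goal; the OR per 10 points of intake is 1.0 to 1.3. Approximately, log OR without intake = 0.30 + ln(OR per 10 points) × shift/10. For 1.2 and 8 points this is 0.30 + 0.182 × 0.8 = 0.446, or OR 1.56. The simulation gives 1.54, slightly lower because odds ratios are not collapsible.

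| OR per 10 points | OR without intake (shift 4 / 8 / 12) | OR with intake |
|---|---|---|
| 1.0 | 1.33 / 1.34 / 1.36 | 1.33 to 1.36 |
| 1.1 | 1.38 / 1.45 / 1.49 | 1.33 to 1.34 |
| 1.2 | 1.44 / 1.54 / 1.65 | 1.34 to 1.35 |
| 1.3 | 1.45 / 1.63 / 1.80 | 1.33 to 1.35 |

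If intake has no effect on diarrhea, the two models agree. The simulation has no path from diarrhea back to intake; such a path could move the estimate in another direction. No comparable calculation was made for mortality or length of stay.

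**The case against.** Much can fairly be said for the plan, and several stronger readings do not stand.

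- A reader might infer that the caloric question cannot be answered at all. It can: the same Table 1 row and the Data analysis section give the mean percentage of goal and the proportion on PN by group, each with a 95% CI. The regression is supplementary.
- A reader might infer that every regression in the protocol carries the fault. The Data analysis section also plans a model of the type of EN chosen on baseline characteristics, without intake. It plans univariate as well as multivariable models for diarrhea, so an IEN/CEN OR not adjusted for intake should already be available.
- A reader might extend the circularity to PN use, or the conflict between text and table to all three rows. PN use is a different quantity from intake, and the statement about baseline characteristics concerns caloric targets only.
- The diarrhea row asks about risk factors, and intake is a plausible one. The primary IEN/CEN comparison is a separate row with no covariates. Calling intake an outright error in the diarrhea row would presume an estimand that the row does not state.
- A reader might go on to ask that NIPPV and vasopressor covariates be restricted to Day 1. Table 1 does not fix their timing, Day 1 values are collected, and the Data analysis section groups patients by whether they received NIPPV. The documents do not support that request.

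All of this narrows the point. None of it defends intake as a covariate in a model of intake, or in the mortality/length-of-stay row, whose stated objective is the IEN versus CEN difference.

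**Conclusion.** The point holds in limited form and should be fixed. The caloric-intake regression is circular as tabulated and conflicts with the text that describes it. This rests on reading the document and on the definition of the outcome, not on the simulation. The near-complete loss of the mode effect (OR 1.57–1.88 falling to 0.99–1.00) is an illustration in which mode acts only through mean intake.

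For PN use, mortality and length of stay, the IEN/CEN estimate is not the total effect, because the model conditions on a post-exposure variable that the protocol treats as a result of mode. In the diarrhea row intake may stay as a candidate predictor, but the adjusted IEN/CEN OR should not be read as the total effect.

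The size of the bias in the diarrhea and mortality models cannot be derived from the documents, and its direction is uncertain if feeds are reduced after diarrhea. The unadjusted primary proportions and the descriptive caloric comparison are untouched, so this does not threaten the primary result.

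**What to change.** 1. Delete daily caloric intake from the covariate lists of the caloric/PN row and the mortality/length-of-stay row of Table 1. For the caloric model this also brings the table closer to the Data analysis text. If a nutritional covariate is wanted, use the admission caloric goal or weight, both already collected.
2. In the diarrhea row, report the IEN/CEN OR from a multivariable model without intake. If intake is of interest as a risk factor, show the intake-adjusted model as a separately labelled secondary analysis. State how daily intake is summarized and that its IEN/CEN coefficient is not a total effect.

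The cost is two table cells edited and a sentence or two added for the diarrhea row. No new data are needed, and each corrected model has one term fewer unless a baseline nutritional covariate takes its place. The change should be recorded before the models are fitted.

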## Abstract

Enteral nutrition (EN) has become the standard of care for nutritional support among critically ill patients. However, little is known about whether continuous delivery (CEN) or intermittent delivery (IEN) is preferable or the consequences of either strategy. This is particularly true for diarrhea, which is understudied but consistently shown to be associated with increased morbidity among critically ill patients. This is a multicenter, retrospective cohort study including critically ill patients greater than 18 years of age, admitted to the Intensive Care Unit in Hamilton, Canada, and prescribed EN for greater than 48 hours. Patients will be divided into IEN and CEN groups based on the nutritional strategy they received during their stay. The primary outcome will be the proportion of patients in each group with diarrhea during their ICU stay, diarrhea will be defined according to WHO criteria. Multivariate logistic regression will be performed to identify the role of covariates in the risk of developing diarrhea. Secondary outcomes will include caloric intake, incidence of ICU-acquired infections, including *Clostridioides difficile*, length of stay, and mortality. This study protocol has been approved by the Hamilton Integrated Research Ethics Board (#16453). The study findings will be disseminated at academic conferences and published in peer-reviewed journals.

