To determine whether IEN or CEN is associated with differences in aspiration pneumonia/pneumonitis	Incidence of aspiration pneumonia/pneumonitis, determined pragmatically by ICU team	NA	The incidence of aspiration pneumonia/ pneumonitis will be computed as the number of new cases during ICU stay divided by the person-time at risk. Descriptive statistics (proportion of patients with aspiration pneumonitis/ pneumonia) and corresponding 95% CI

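### C. difficile infection has no onset rule, and no infection or aspiration outcome is tied to the start of feeding, so early events can be attributed to IEN or CEN

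*Protocol article*

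**What the plan says.** **Bloodstream infection.** Table 1 counts "Incidence of positive blood cultures drawn at least 48 hours after admission", and Data collection lists "bacteremia greater than 48 hours after admission". The rate in Table 1 uses new cases arising in the ICU over person-time at risk.

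**CDI.** The Abstract announces "Secondary outcomes will include caloric intake, incidence of ICU-acquired infections, including" C. difficile. The Table 1 objective reads "To determine whether IEN or CEN is associated with ICU-acquired bloodstream infection or *Clostridium difficile* infection". The outcome cell of that row then defines blood cultures only. The new-case rate in the row is written for bloodstream infection. CDI appears only in "Descriptive statistics (proportion of patients with ICU-acquired bloodstream infection or *C. difficile infection*) and corresponding 95% CI". Data collection and Outcomes list CDI without any time limit.

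**Aspiration.** The outcome is "Incidence of aspiration pneumonia/pneumonitis, determined pragmatically by ICU team". Table 1 gives two measures: a rate, limited to new cases arising in the ICU, and a proportion of patients, which has no such limit.

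**Comparison.** The covariate cell is NA in both Table 1 rows. Data analysis assigns patients to IEN or CEN from the feeding received over the study days. It analyses hospital-acquired infections per person-time in each group and does not say when the risk period starts. The caloric and parenteral nutrition outcomes, by contrast, are timed from initiation of CEN or IEN.

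**The concern.** There are two separate gaps.

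The first is at ICU admission. The plan means to count ICU-acquired CDI but gives no rule that separates it from CDI already present on arrival. Participants does not exclude patients admitted with CDI. The aspiration proportion has the same gap.

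The second is at the start of feeding. An event that arises in the ICU before the first feed cannot be an effect of the feeding mode. Nothing in the plan keeps such an event out of the IEN versus CEN comparison for bloodstream infection, CDI or aspiration. It is attributed to whichever group the patient later joins. If person-time runs from ICU admission, the unfed time goes to that group as well.

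Balanced early events pull a real difference towards no difference. Unbalanced early events create a difference where there is none. With no covariates in these rows, nothing later in the analysis corrects either effect.

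**Working it through.** **The plan's own figure.** The plan has no figure for these outcomes. Its one computed design figure is 455 per group for diarrhea (25.1% versus 17.5%, two-sided alpha 0.05, power 0.8). With p̄ = 0.213, the pooled formula gives

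n = [1.960·√(2·0.213·0.787) + 0.842·√(0.251·0.749 + 0.175·0.825)]² / 0.076² = (1.135 + 0.485)² / 0.005776 ≈ 454.4, rounded up to 455.

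It reproduces and is not affected by this point.

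**The rules side by side** (Table 1, Data collection, Outcomes, Data analysis)

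| Outcome | Hours from admission | Limited to new ICU cases | Tied to start of IEN/CEN | Covariates |
|---|---|---|---|---|
| Bloodstream infection | 48 | yes | no | NA |
| CDI | none | by label only, no rule | no | NA |
| Aspiration | none | rate yes, proportion no | no | NA |
| Caloric intake, parenteral nutrition | not applicable | not applicable | yes | listed |

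**Three patients under these rules**

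1. A first C. difficile test is positive on the day of ICU admission. The label says ICU-acquired, but no stated rule removes the patient from the CDI proportion.
2. Aspiration first occurs on ICU day 2 and feeding starts on day 3. This is a new ICU case, so it enters both the rate and the proportion of the later feeding group.
3. A blood culture is drawn at 72 hours and feeding starts afterwards. It passes the 48-hour rule and still precedes exposure. The 48-hour rule runs from admission, so extending it to the other outcomes would not close the second gap.

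**Illustration only.** The document gives no CDI or aspiration rates, so every input here is an assumption. Let r be the true risk after feeding starts and q the share of patients with a counted early event. Then the observed risk is q + (1 − q)·r.

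*Same q in both groups*, with r = 5% (CEN) and 10% (IEN), a true risk ratio of 2.0. Power assumes 250 per group, that is, the roughly 500 expected patients taken as the total and split evenly.

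| q | CEN observed | IEN observed | Risk ratio | Power |
|---|---|---|---|---|
| 0 | 5.0% | 10.0% | 2.00 | 0.57 |
| 2% | 0.02 + 0.98·0.05 = 6.9% | 0.02 + 0.98·0.10 = 11.8% | 1.71 | 0.47 |
| 5% | 0.05 + 0.95·0.05 = 9.75% | 0.05 + 0.95·0.10 = 14.5% | 1.49 | 0.37 |
| 10% | 0.10 + 0.90·0.05 = 14.5% | 0.10 + 0.90·0.10 = 19.0% | 1.31 | 0.27 |

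With r = 4% and 8%, the risk ratio falls from 2.0 to 1.66, 1.43 and 1.26.

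*Different q, no true effect* (r = 5% in both groups):

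- q = 2% versus 5%: 9.75 / 6.9 = 1.41
- q = 5% versus 10%: 14.5 / 9.75 = 1.49

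For the two proportions, q can include cases present at admission. For the aspiration rate it covers only ICU cases before feeding.

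**The case against.** **The aspiration rate is already restricted.** A reader might infer that a patient admitted because of aspiration counts against a feeding group in every measure. The document does not support that for the rate, because a case present on arrival is not a new ICU case. It also never calls aspiration ICU-acquired. This part of the objection stands. What remains for aspiration is the unrestricted proportion and the cases that arise in the ICU before feeding.

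**The intent for CDI is clear, and detail may sit elsewhere.** An article can leave an hour threshold to a fuller document, and the pilot on 40 charts is meant to refine reports and case report forms. That would answer the point if the article were silent on onset for every infection. It is not silent. It fixes a 48-hour rule for one infection in the row and none for the other, although the objective names both. It also times other outcomes from feed initiation but not these.

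**These are secondary, descriptive outcomes.** They are secondary. They are not purely descriptive: the objectives ask whether feeding mode is associated with these events, and Data analysis plans a significance test between groups.

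**The numbers are assumed.** This is correct. A reader might also infer which mode is disadvantaged, since the Introduction reports a guideline against IEN in high-risk patients. That makes imbalance plausible. It does not establish its direction or size.

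**Conclusion.** The point holds in limited form. CDI is labelled ICU-acquired without any onset criterion, so CDI present at ICU admission can be counted. The aspiration rate nominally leaves out cases present on arrival, but the proportion beside it does not. None of bloodstream infection, CDI or aspiration is anchored to the start of IEN or CEN, so ICU events before feeding go to the later feeding group in comparisons without covariates.

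The size cannot be derived from the document. Under the assumptions shown, balanced early events of 2% to 10% reduce a true risk ratio of 2.0 to between 1.71 and 1.31, and unbalanced ones give 1.41 to 1.49 where there is no effect. These figures show how the bias works; they do not estimate it. The primary diarrhea outcome and its sample size are untouched. The change is worth making before data extraction is complete.

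**What to change.** Restrict the IEN versus CEN comparison of these outcomes to EN-fed patients. The cohort also includes patients on non-invasive ventilation with no EN prescription, for whom a feeding anchor is undefined. Then state in Table 1, Data collection and Outcomes:

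- **CDI:** count only if the first positive specimen is at least 48 hours after ICU admission and after EN initiation.
- **Bloodstream infection:** keep the 48-hour rule and also require onset after EN initiation.
- **Aspiration pneumonia/pneumonitis:** in both the rate and the proportion, count only if first documented after the time of EN initiation. Events later on the first feeding day stay in.
- **Baseline:** record CDI or aspiration present before these points as baseline variables.
- **Person-time:** start it when events become countable. For bloodstream infection and CDI this is the later of 48 hours and EN initiation; for aspiration it is EN initiation.

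The cost is mainly wording. Feasibility says that microbiology and EN prescription data are readily accessible and that aspiration is reviewed by hand, so the main addition is a documented date and time for aspiration. The downside is fewer counted events and less precision.
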